## Abstract

**Aim:** To determine the effectiveness of capacity building program on palliative care (PC) in enhancing the capacity of the primary health care workers in need assessment and symptom management of cancer patients.

**Background:** In India, less than one percent of people living with cancer have access to palliative care since most are from low- and middle-income groups. Accredited social health activist (ASHA) and primary health care workers are grassroots workers who are the first contact with family members and are seldom aware of PC in India. It is essential to train them to give practical and efficient care to needy people.

**Design:** A quasi-experimental design with follow-up will be conducted using an evaluative approach.

**Methods:** The study population consists of 1440 Primary Health Care Workers (staff nurses, ANMs, and ASHA workers) of three taluks of Udupi District, Karnataka State, India. Training on PC will be provided for ASHA workers for one day and ANM/Staff nurses for three days. After their training, they are expected to demonstrate the gain in knowledge & skill in providing PC for cancer patients by identifying and implementing PC services using a mobile app at the primary healthcare level.

**Discussion:** Palliative home care can give comfort and reduce patients’ financial burden, and this training may help to improve the quality of life of needy patients.

**Impact:** If this palliative care training program succeeds, it can be integrated into the healthcare continuum, making it an essential component of primary healthcare delivery to achieve universal health coverage. Moreover, home-based PC supports patients who want to die at home even though it reduces hospital stay costs.

**Trial registration:** CTRI/2020/04/024792.

## Introduction

The GLOBOCAN 2020 estimated 19.3 million new cases of cancer and 10 million bereavements due to cancer in 2020 (
Sung *et al.*, 2021). Both private and public primary care facilities and public secondary facilities are inadequately prepared to address the burden of non-communicable diseases (NCDs) in India (
Krishnan *et al.*, 2021). Inequitable access to palliative care is one of the greatest disparities in global health care and lack of access to palliative care in low- and middle-income countries (LMICs) has led to a huge burden of preventable suffering (
Knaul, Bhadelia, Rodriguez, Arreola-Ornelas, & Zimmermann, 2018). Although there are several initiatives towards palliative care development in India, palliative care access is significantly limited to a small population (
Rajagopal, 2015). Improving palliative care education and awareness of healthcare professionals in India might be an effective strategy towards facilitating palliative care access (
Glass *et al.*, 2020).

According to the oncology-based palliative care development project designed for the north-eastern region of India, developing oncology-based palliative care in India could demonstrate the implementation of a local version of the WHO model which emphasizes highlights the strengths of integrating palliative care within the cancer care programs right from its inception. It highlights the supportable public health care services present in comparison with the funded initiatives. This WHO model emphasizes the usefulness of this for LMIC countries with similar health and socio-cultural contexts (
Vallath *et al.*, 2021). In this regard, India requires the development of clinical guidelines according to the local needs for palliative home care ensured quality and uniform delivery of clinical services (
Jeba *et al.*, 2020).

Helping native populations to institute community-led palliative care programs is the best way to address the lack of accessibility and sustainability of appropriate palliative care services at the end of life to most people in the world which is a complex task. This requires great rigor in both stages of conceptualization and implementation (
Kumar, 2020).

Capacity building of community health care workers in Brazil yielded in the successful conduct of the home visits and screening for risk factors in the elderly population (
Neto *et al.*, 2021). Nurses play a vital role in the care of patients especially caring for those who are dying, hence it is imperative for them to know the best principles of palliative care (
Sadhu, Salins, & Kamath, 2010). The role of the family in the care of chronically ill patients is significant and they should be socially supported and empowered to cope with the situation (
Philip, Philip, Tripathy, Manima, & Venables, 2018).

Availability of the digital health device for the reporting of the symptoms in patients with cancer to attend palliative care needs results in the reduction of the number of emergency department visits and thereby reduced health care costs (
Bhargava *et al.*, 2021). There is promising evidence to use mobile health apps to provide expanded and enhanced health care services to individuals and communities, taking advantage of the growing usage of mobile phones among diverse populations (
Källander *et al.*, 2013).

An India-specific document and a supportive quality development program suggested the need for additional training of palliative care providers towards the implementation of palliative care (
Salins, Johnson, & Macaden, 2017). Despite having a robust palliative care policy in India, a study carried out through direct fieldwork and interviews with the health care workers reported a lack of public health approach to end-of-life care. This study further suggested the need for increased participation of the local and political readiness to implement palliative care delivery effectively (
Jayalakshmi & Suhita, 2017).

National Health Systems Resource Centre (NHSRC) in India at present is associated with the preparation and training focussing on the Health care workers including ASHA, ANM to Medical Officers at Health and Wellness Centers across India (
Centre, 2021b). To build a liaison between the community and public health system in India, under National Rural Health Mission there are Accredited Social Health Activists (ASHA) selected from the village who is planned to gather individuals’ understanding of health rights and empower them to get to their privileges (
Centre, 2021a).

## Background

The Global Atlas reveals that over 56.8 million people need Palliative Care (PC) worldwide (Organization). Adults over 50 years’ account for 67.1%, with children accounting for 7.1%. Among the adults, the largest single disease group needing PC is cancer (28.2%). Among children, cancer accounts for 4.1% of PC needs. Across resource settings, 76% of adults and >97% children (0-19 years) are from low and middle-income countries (LMIC). The regional distribution shows that 17.1% of adults and 19.5 of children needing PC are from the South East Asian Region (SEAR). SHS amenable to PC interventions is expected to increase by 87% by 2060 (
Connor & Sepulveda Bermedo, 2018).

One of the key objectives of the National Programme for the prevention and control of cancer is establishing and developing a capacity of health care workers for planning health care activities including home care and palliative care (
DIRECTORATE GENERAL OF HEALTH SERVICES & Welfare). One of the aims of the national palliative care program is to improve the capacity among health care workers to provide palliative care service delivery within government health programs (
DIRECTORATE GENERAL OF HEALTH SERVICES & Welfare, 2012). Trained ASHA workers in their respective localities were able to identify people with psychiatric disorders and refer them to advanced care settings for further management (
Ibrahim *et al.*, 2021). Palliative care intervention that influences the inclusion of community health workers could serve as a feasible model for expanding the reach of palliative care to rural underserved patients (
Qanungo *et al.*, 2021). Rethinking of normal hospice services is recommended as they can participate in community capacity building in integrating palliative care (
Paul, Cree, & Murray, 2019).

The process of translating a palliative care plan into action requires strong leadership, competent management, political support, and integration across all levels of care (
Kar, Subitha, & Iswarya, 2015). CanSupport a multidisciplinary team approach reported that a home-based care model could be more approachable to the patients in India especially during end-of-life care or among patients with a chronic life-limiting illness. It is even reported in Can Support that the successful implementation could reduce the number of hospital visits, and finally reduce the total cost of the hospital by providing the best possible care by the trained health care people (
Yeager *et al.*, 2016).

Developing policies concerning inculcating family-centered palliative care and end-of-life care within the nursing curriculum could help in promoting the nurse-led community models to address the palliative and end-of-life service care in India (
Ramasamy Venkatasalu *et al.*, 2018).

There is a disparity between the number of patients who could be benefiting from palliative care and the number of palliative care specialists. It is a vital aspect to improve basic palliative care delivery skills, identification of patients in need, and appropriate referral to palliative care specialists to effectively integrate the same into primary health care (
Gorman, 2016).

Organizing home-based palliative care services as a quality improvement project resulted in a consistent increase in the frequency of home visits, better documentation, coordination, and accountability. Interdisciplinary team coordination helped to develop trust and a better understanding of collaborative research work (
Viswanath *et al.*, 2021).

The implementation of the Neighbourhood Network in Palliative Care (NNPC) in the Indian state of Kerala included the trained volunteers who were encouraged to form groups of 10-15 community volunteers, to identify the problems of the chronically ill people in their area and organize appropriate interventions. This NNPC service was reported as a cost-effective option for most developing countries to develop much-needed sustainable services for chronically ill and dying patients. In 2010, this network saw over 2500 patients per week and attained coverage of over 60% in many areas with NNPC groups that trained doctors and nurses support (
Sallnow, Kumar, & Numpeli, 2010). A home-based palliative care program was perceived to improve the lives of patients and their caregivers despite the challenges of maintaining a volunteer-led program (
Philip, Venables, Manima, Tripathy, & Philip, 2019).

Family carers suggested having a minimum number of carers involved in care, increasing or ensuring personal continuity, and maximizing the informational and organizational aspects of care could lead to a more positive experience (
Seamark *et al.*, 2014). There was some evidence of increased patient satisfaction with home-based end-of-life care (
Shepperd, Wee, & Straus, 2011).

A structured training program on symptom management kit for primary caregivers of cancer patients receiving home care was conducted at CMC, Vellore, India reported that, of the primary caregivers, 96.7% used a symptom management kit and received training resulted in a reduction of hospital visits for acute symptoms reduced by 80%; 90% were satisfied with the training received; 73% stated it was not a burden to treat the patient at home. This study further reported that the program and the kit were reported to be perceived favorably by caregivers from diverse backgrounds. Rural backgrounds and illiteracy were not barriers to acceptance of home-based palliative care (
Chellappan, Ezhilarasu, Gnanadurai, George, & Christopher, 2014).

The mobile phone was chosen because it helps CHWs achieve better results in their daily activities. The five main mobile health functions that support frontline health workers (FHWs) in providing adequate care to their communities are data collection and reporting, decision-making resources and training, emergency referrals, warnings and reminders, and supervision. also, mobile data collection increases data collection promptness, decreases error rates, improves data completeness (
Agarwal, Perry, Long, & Labrique, 2015).

Studies have shown that the training programs conducted for primary caregivers help provide palliative care. It also showed that most of them were satisfied with the training provided (
Chellappan *et al.*, 2014). A study was carried out to examine the effectiveness of a holistic capacity-building program for volunteers in community-based end-of-life care (EoLC). Following the screening, 88 of the 171 candidates completed core competency training, with 53 continuing to volunteer for the next six months. Their end-of-life care competence, self-care understanding, and death work competence improved significantly following training and remained stable at the 6-month follow-up (
Wang, Chan, & Lou, 2020).

A cross-sectional interventional study was conducted in Delhi on the effectiveness of the certificate course on essentials of palliative care program among 29 health care professionals. The study revealed that, in the pretest, about 24.1% of them had good knowledge and which was improved to 82.8% after the training. 62.1% had average knowledge, and only 13.8% had poor knowledge. Since completing the program, participants improved their communication skills, symptom management, negative news breaking, and pain assessment (
Bhatnagar & Patel, 2018). Studies also have reported that the scope and coverage of palliative care can be improved by providing training for medical officers and health care professionals and sensitizing the public through an awareness campaign (
Kar *et al.*, 2015).

This current project on improving the symptom assessment and management is intended to help to improve the knowledge and practice of primary health care workers on palliative care for need identification in the community.

## Protocol

### Research objectives

The objectives of the study are to:
•Assess the knowledge on palliative care pre and post-education among PHCWs by a survey study using a structured knowledge questionnaire.•Assess the attitude on palliative care pre and post-education among PHCWs by a survey study using a structured attitude questionnaire.•Assess the interpretive skill on palliative care pre and post-education among PHCWs by a survey study using a structured questionnaire on interpretive skill.•Identify the challenges and barriers for delivery of palliative care at the community level through qualitative interviews of the focused groups using an interview topic guide.

### Study design

The impact of palliative care education on skills, attitude, and interpretive skills will be known through a Quasi-experimental design study having a pre-/post-intervention assessment of PHCWs (staff nurses, ANMs, and ASHA workers). The interventions will be the training of PHCWs on community palliative care and the implementation of a palliative care mobile app in the community. The outcome assessed is improvement in palliative care knowledge and enhancement of identification of palliative care needs in the community.

### Research setting and study population

The study will be conducted at 59 primary health centers and 316 sub-centers in the rural locations of a district in Southern India. The study participants will be eligible and consenting registered ASHA workers (1011) and Primary Health Care Workers who are working under Primary Health Centers and Sub Centers (staff nurses/ ANMs or Junior health workers/Assistants = 429).

### The rationale for selection of the participants

Cancer patients often experience financial constraints concerning cancer treatment in India (
Oswal *et al.*, 2021). As primary health care centers throughout the country deliver the essential medical assistance and the primary health care workers are the grass root level workers who work with the rural population closely, the national policy on palliative care emphasizes training the health care workers and providing accessible care to the cancer patients at the community level (
DIRECTORATE GENERAL OF HEALTH SERVICES & Welfare, 2012). World Health Organization (WHO) emphasizes all countries integrate palliative care at the primary health care level (
Organization, 2018).

Thus the total population of PHCWs & ASHAs in the selected District is
**1440** excluding vacancies (
Figure 1).

**Figure 1. f1:**
[figure not shown]
Number of SN/ANM/ASHAs working in PHC/SCs three taluk of selected District.

### Inclusion criteria

PHCWs working as Staff nurses, Auxiliary Nurse Midwives or Junior Health Assistants, and ASHA workers who are trained female community health activists who are selected from the same village to be an interface between the community and public health system working under PHC/SCs of Selected District will be the participant in this project. These workers who are willing to participate in the study will be trained to identify the symptoms requiring palliative care for children and adults with cancer and provide palliative care for the same.

### Intervention

**Training**

The palliative care module will be prepared and training will be provided to the PHCWs to sensitize them concerning the concept of palliative care. A series of education will be planned and it will be conducted through workshops.

### Development of palliative care module for PHCWs

The palliative care module for PHCWs will consist of:
•Introduction, definition, principles of palliative care•The role of a nurse in palliative care•Symptoms assessment, and management such as pain, dyspnoea, nausea and vomiting, diarrhea, constipation, wounds, edema, skin problems, anorexia, cachexia, fever.•Practical sessions on colostomy care, nasogastric tube insertion and tube feeding, urinary catheterization and catheter care, oral care, tracheostomy care, wound care, prevention of bedsores, subcutaneous injection procedures, lymphedema care.

### Outline for mobile app

To enable the functioning and tracking, an Android-based Application will be developed for usage by the PHCWs and health service providers. The Android App would contain the following functional modules
i.Knowledge center that includes the information about palliative care needs, symptoms identification management. The content would contain Images, Videos, and links to online resources.ii.Module to register, create and update the patient dataiii.Search and generate alerts for patient monitoring by Health workersiv.Option to synchronize the data with the Health center for tracking purpose

The overall application structure will be as depicted in
Figure 2.

**Figure 2. f2:**
[figure not shown]
Application architecture.

The Public Health Care Worker (PHCW) will have an Android-based application on their mobile devices. The Android App features are as per the details outlined in
Figure 2. The App can store the data locally and forward the details to the central data repository for monitoring and reporting purposes. Using the App on their mobile device, health worker refers to the training materials available in the App and also record the patient details of the locality they cover. The patient data collected by the health workers on the Android App will be transferred to the central data store by the health worker using the data synch option of the App.

On the Health Service Provider section, the application would contain a Web Interface, Web services, and the Central Data-store. The Web services section would help in registering the health worker details and configure the App on the mobile device of the health worker for the intended functioning (
Table 1). The web services will also enable data synchronization between the mobile device and central data store. Central Data-store acts as the repository of data collected from all the health workers and acts as the basis from which various findings from the study in the form of different reports can be generated. The Web interface provides the mechanism for the study managers at the Health Service Provider section to monitor the system and generate reports from the system.

**Table 1. T1:** Outline for mobile app.

PHCWs details to be entered in mobile app	Identification of symptoms and management details
1. Login → User ID for ASHA/ANM/Staff Nurse (ID should begin from 01 for each category) → Password	1. Patient Id → Name of the patient → Age → Gender → Name of the city/village → Disease condition Symptom
2. Name of Taluk: Site 1, Site 2, and Site 3	2. No. of cases identified by the PHCW
3. Name of ASHA/ANM/Staff Nurse	3. No. of symptoms identified
4. Gender	4. No. of episodes occurred for each patient
5. Phone number	5. No. of follow up done
6. Name of health center: PHC/CHC/SC	6. Symptoms managed
	7. No. of cases referred
	8. No. of deaths → Case closed (In case of death)
	9. Feedback by patient and family members

### Expected outcome

The expected outcome of this study is to identify the impact of palliative care training in improving palliative care knowledge and their ability to assess palliative care needs in the community among PHCWs. To explore views of PHCWs on the facilitators and barriers for palliative care delivery in the community.

### Recruitment, consent, and data collection

All regulatory and administrative approvals will be sought. After explaining the procedure and objectives of the research project, written informed consent from all the participants will be obtained. The questionnaires are prepared in English and Kannada. The outcome of the project will be measured by using demographic proforma, knowledge questionnaire, attitude scale, skill checklist, and validated set of questions on focus group discussion (
Figure 3).

**Figure 3. f3:**
[figure not shown]
Schematic representation of data collection process.

### Data collection instruments

The questionnaires to be used in this project include demographic proforma, structured knowledge questionnaire on palliative care, attitude scale, and checklist for skill assessment.
a)The demographic proforma will be used to assess the demographic characteristics of the PHCWs such as age, gender, marital status, religion, monthly income, designation, place of work, years of experience, and area of working.b)A structured knowledge questionnaire will be used to assess the existing knowledge on palliative care among PHCWs. The questionnaire includes the areas like essential elements of palliative care, the role of the palliative care team, the role of the nurse in palliative care, nursing ethics, various symptom identification and management, communication skills, end of life care, grief & bereavement care by using an MCQs and dichotomous items and also open-ended items. The knowledge score for staff nurses, ANMs contains 30 MCQs. The scores are categorized as 26 and above (75%), 18 to 25 (50 to 74%), 17 and below (less than 50%), which indicates good knowledge, average knowledge, poor knowledge, respectively. The knowledge score for ASHA workers contains 22 items. The scores are categorized as 17 and above (75%), 11 to 16 (50-74%), ten and below (less than 50%), which indicates good knowledge, average knowledge, and poor knowledge, respectively.c)Attitude scale: The attitude of PHCWs will be measured by using the Likert scale. The scores are categorized into positive and negative attitude scores. Total 30 items with 5 Likert scores are included. The positive score of attitude scale for staff nurses, ANMs ranges from 91 to 150, and the negative score ranges from 30 to 90. For ASHA workers, the attitude scale contains ten items with five Likert scores. The positive score of the attitude scale for ASHA workers ranges from 31 to 50 and the negative score ranges from 10 to 30.d)Skill checklist: Various skills will be assessed by using a skill checklist during the training programs like colostomy care, nasogastric tube insertion and tube feeding, urinary catheterization and catheter care, oral care, tracheostomy care, wound care, prevention of bedsores, subcutaneous injection procedures, lymphedema care. The checklist for skill assessment has yes/No questions. The research team will observe the participants using the checklist while performing the procedures to assess their skills.e)Focus Group Discussion (FGD) among PHCWs from selected PHCs: questions will be asked regarding the facilitators and barriers in providing palliative care at the end of one year after implementing the palliative care training program. Thematic analysis will be used to evaluate the outcome of the focus group discussion.

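### For staff nurses and ANMs, the knowledge test's item count, its cut-offs of 26 and 18, and the 75% and 50% attached to them do not agree

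*Protocol article*

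**What the plan says.** The Protocol article sets the scoring rule under Data collection instruments, item b. For the nursing cadres it states: "The knowledge score for staff nurses, ANMs contains 30 MCQs". The bands follow: "The scores are categorized as 26 and above (75%), 18 to 25 (50 to 74%), 17 and below (less than 50" per cent, labelled good, average and poor in that order.

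For ASHAs it states "The knowledge score for ASHA workers contains 22 items", with bands "The scores are categorized as 17 and above (75%), 11 to 16 (50-74%), ten and below (less than 50" per cent and the same three labels.

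The same item describes the questionnaire as built "by using an MCQs and dichotomous items and also open-ended items". It gives no marks per item and no maximum score for either test.

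Research setting and study population gives the number of workers in the nursing cadres: "staff nurses/ ANMs or Junior health workers/Assistants = 429". Knowledge is the first research objective, and Study design names it as an outcome: "The outcome assessed is improvement in palliative care knowledge and enhancement of identification of palliative care needs in the community".

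**The concern.** A reader who takes 30 items at one mark each finds that none of the three nurse/ANM bands carries the right percentage, and that both limits sit above where the percentages would put them. The ASHA rule two sentences later has no such fault.

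The bands are the only interpretation of the knowledge score that the article offers. The Background cites an earlier evaluation of palliative care training that reported its result as the share with good knowledge before and after the course, so this study may well be reported the same way. If the cut-offs are wrong, the proportions with good and poor knowledge among nurses and ANMs would not mean what their labels say.

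**Working it through.** **Inputs.** From Data collection instruments, item b: 30 items with limits 26 and 18 (nurses/ANMs), 22 items with limits 17 and 11 (ASHAs), and percentages of 75 and 50 for both. Assumption: one mark per item, which the text implies but does not state.

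**Rule.** The lowest score in a band is the percentage times the maximum, rounded up to a whole mark.

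**Step 1, ASHA test: the plan's figures reproduce.**
- Good: 0.75 × 22 = 16.5, so from 17. Average: 0.50 × 22 = 11, so from 11.
- As percentages: 17/22 = 77.3%, 16/22 = 72.7%, 11/22 = 50.0%, 10/22 = 45.5%. All fit their labels.

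**Step 2, nurse/ANM test on 30 marks: the plan's figures do not reproduce.**
- Good: 0.75 × 30 = 22.5, so from 23 (printed 26). Average: 0.50 × 30 = 15, so from 15 (printed 18).

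| Printed limit | Share of 30 | Printed label |
|---|---|---|
| 26 (lowest good) | 86.7% | 75% |
| 25 (highest average) | 83.3% | 74% |
| 18 (lowest average) | 60.0% | 50% |
| 17 (highest poor) | 56.7% | below 50% |

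Both limits are 3 marks too high. The scores that change band are 23-25 (76.7-83.3%, average instead of good) and 15-17 (50.0-56.7%, poor instead of average).

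**Step 3, could another maximum M explain 26 and 18?**
- Read strictly, 26/M ≥ 0.75 needs M ≤ 34, while 17/M < 0.50 needs M ≥ 35. No M meets both. At 34, 17/34 = 50.0% is labelled below 50%. At 35, 26/35 = 74.3% is labelled 75%.
- With rounding to the nearest mark, halves up, M = 35 gives 26.25 → 26 and 17.5 → 18, which are both printed limits. M = 34 gives 26 and 17, and M = 36 gives 27 and 18.
- The same rounding on 22 items gives 16.5 → 17 and 11 → 11, so the ASHA limits cannot show which rounding was used.

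**Step 4, size if the maximum is 30.** The documents give no score distribution. As an illustration, assume independent items with the same chance of a correct answer, and take binomial tail probabilities.

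| Chance correct per item | Good at ≥26 | Good at ≥23 | Poor at ≤17 | Poor at ≤14 |
|---|---|---|---|---|
| 50% | 0.0% | 0.3% | 81.9% | 42.8% |
| 60% | 0.2% | 4.4% | 42.2% | 9.7% |
| 70% | 3.0% | 28.1% | 8.4% | 0.6% |
| 75% | 9.8% | 51.4% | 2.2% | 0.1% |
| 80% | 25.5% | 76.1% | 0.3% | 0.0% |
| 85% | 52.4% | 93.0% | 0.0% | 0.0% |

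**The case against.** The strongest reply is that the cut-offs may be sound and the item count misprinted. No maximum is stated, and the questionnaire is said to contain dichotomous and open-ended items as well, so 30 multiple-choice items need not be the whole score. A maximum of 35 with ordinary rounding yields all four printed limits, two for each cadre. This stands. It means that rounding could account for the cut-offs at some maximum, though not at 30.

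A reader might infer that nurses and ANMs are in fact put in the wrong band and judged more harshly than ASHAs. The documents support that only if the maximum is 30, which they do not establish. The illustrative proportions in Step 4 carry the same condition.

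A reader might also infer that comparisons or pooling with ASHAs would be biased. No such analysis is planned: the cadres take different tests after training of different length (three days against one, in the Abstract). Nor does Statistical analysis say that the bands will be tested, and the sample size rests on the proportion of workers expected to implement the programme, not on the proportion with good knowledge. A pre/post comparison of raw scores does not use the bands at all.

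None of this removes the contradiction. Under either reading at least one printed number is wrong, and no other section settles which.

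**Conclusion.** The nurse/ANM scoring rule contradicts itself as printed, and the ASHA rule beside it does not. How much this matters depends on the unstated maximum.

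- **Maximum 30, one mark per item:** six scores (15, 16, 17, 23, 24, 25) fall in a band that contradicts its percentage. For up to 429 workers, the share with good knowledge is understated and the share with poor knowledge overstated. The gap can be large: in the illustration, 9.8% against 51.4% good when each item has a 75% chance of a correct answer.
- **Maximum about 35:** the item count is the main error and the consequence is slight. At 35, only a score of 26 (74.3%) is mislabelled.

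The effect is confined to the descriptive good/average/poor reporting. Since knowledge is a named outcome and the repair is trivial, the rule should be corrected before it is used.

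**What to change.** Before any scores are banded, state the maximum mark of the nurse/ANM test, with the marks given to each item type, and only then set the cut-offs. Derive them with the percentage rule used for ASHAs, so that good is at least 75% of the maximum and poor is below 50%:

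- maximum 30: good 23 or more, average 15-22, poor 14 or less;
- maximum 35: good 27 or more, average 18-26, poor 17 or less, with the item count corrected as well.

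The ASHA limits stay at 17 and 11. Resetting the limits to 23 and 15 without first confirming the maximum could replace cut-offs that were properly derived. The cost is a one- or two-sentence correction to the scoring rule, with no new data. Making it before banding avoids any suspicion that the cut-offs were chosen after the scores were seen.
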